### Participants

3.2

Women between 18 and 60 years of age, diagnosed with chronic non‐specific neck pain (as described by the IASP) and/or diagnosed with TMD according to the Diagnostic Criteria for Temporomandibular Disorders—DC/TMD (Dworkin, 2014) will be included. In addition, a baseline pain score of at least 30 points on a 0 to 100 visual analogue scale (VAS) will be required. Participants with severe pathologies (red flags) related to neck pain, reporting comorbidities (e.g., fibromyalgia), diagnosed with psychiatric disorders, and/or who received therapy within 3 months before study entry will be excluded. All participants will complete the Physical Activity Readiness Questionnaire (PAR‐Q+) to assess readiness to exercise. The Central Sensitization Inventory (CSI) recommended for patients with chronic pain will also be applied. The CSI is an easy‐to‐apply self‐report questionnaire that tracks and assesses symptoms related to overall sensory disturbances (Mayer et al., 2012).

This exploratory clinical trial aims to gather preliminary data on the safety and potential efficacy of a single bout of exercise for individuals with TMD and neck pain. Given the exploratory nature of this study, a formal sample size calculation was not conducted. Instead, the sample size was determined based on practical and logistical considerations. This exploratory study pilot will initially target 30 participants (15 per group), aiming to gain insights and assess feasibility. Based on the targeted sample size and a clinically important difference of 19 points (on a 0–100 pain scale) (Calixtre et al., 2020) with a standard deviation of 20, the study has an estimated 71% power to detect a large effect size (ES, Cohen's *d* = 0.95) using a significance level of 0.05. The recruitment rate of participants, availability of the research team, time, and resources were considered for the targeted sample size. The data collection is expected to be finished by the end of 2025. The results of this study will help to design and calculate sample sizes for future studies.

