### Allocation concealment

3.3

All participants will be randomly assigned to one of the treatment groups: neck motor control exercises or AEs by using an automated system hosted on a web platform. The randomization sequence will be stratified by chief complaint (neck pain or jaw pain) and age (18–30, 31–45, 46–60) and generated by an external party using a randomization website. The sequence generated will be automatically programmed in REDcap to allow the allocation concealment of the sequence.

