### Analyses plan

3.7

All analyses will be performed by the statistical program SPSS version 26 (IBM Corp., Armonk, NY, USA) and STATA v.17 (StataCorp, College Station, TX, USA). The Shapiro–Wilk test and visual inspection of histograms and graphs will be used to verify the normality of the data. Then, descriptive statistics will be performed to characterize the sample and explore variables. The results will be presented as mean and standard deviation when the variables are normally distributed, or as median and interquartile range when the data distribution is not normal. A 95% confidence interval will be adopted. *P*‐values will be interpreted based on Sterne and Smith to determine the evidence against the null hypothesis (Sterne & Smith, 2001).

To accomplish objective (1), which is to assess the effects of a single bout of neck motor control exercises and aerobic training exercises on pain intensity, PPT and PPTo in participants with TMD and neck pain, further inferential analyses will include separate mixed‐effects models (random effect for repeated measurements per participant) for each outcome to assess the effect of the intervention (groups) over time and adjusted by other covariates. First, a fixed‐effects model for each outcome at the final evaluation that includes only the intervention groups and baseline score will be created. Then, mixed‐effects models (random effects for repeated measurements per participant and groups (intercept and slope) will be tested. Finally, these models will be expanded to include covariates (e.g., demographics, psychosocial variables). Models will be compared using the Akaike information criterion (AIC) and the Bayesian information criterion (BIC). The covariates may be dropped from the models if not required for model fit based on AIC and BIC. Model estimates and associated 95% confidence intervals (CI) will be reported.

To accomplish objective (2), the EIH response will be calculated in absolute (raw score) and relative (percentage) changes by subtracting the post‐exercise PPT and PPTo values from the pre‐exercise values. Further exploratory analyses will also be performed with mixed‐effects models considering EIH as an outcome to compare the time points of treatment (beginner, intermediate and advanced training) and group treatment.

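### Chief complaint and age band stratify the randomisation, but no model guarantees them, and covariates may be dropped outcome by outcome on AIC/BIC before ordinary 95% intervals are reported

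*Protocol article*

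**What the plan says.** Protocol article, Allocation concealment (3.3): "The randomization sequence will be stratified by chief complaint (neck pain or jaw pain) and age". With two complaint levels and three age bands there are six strata.

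Protocol article, Analyses plan (3.7), objective 1: each outcome is modelled separately. The sequence opens with a fixed-effects model "at the final evaluation that includes only the intervention groups and baseline score will be created", then moves to mixed-effects models. Next comes an open list: "Finally, these models will be expanded to include covariates (e.g., demographics, psychosocial variables". Models are compared on AIC and BIC, and "The covariates may be dropped from the models if not required for model fit based on AIC and BIC". Estimates with 95% confidence intervals are then reported, with no allowance for the selection. No sentence places chief complaint in any model. Age could enter as a demographic, but nothing ensures it.

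Protocol article, Participants (3.2): the trial is described as exploratory, without a formal sample size calculation, with 15 women per arm. For "a clinically important difference of 19 points" on the 0–100 pain scale, the article adds: "with a standard deviation of 20, the study has an estimated 71% power to detect a large effect size" of d = 0.95, "using a significance level of 0.05".

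**The concern.** Two separate problems follow, and they act in opposite directions on different models.

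- **Selection.** Choosing covariates by fit and then reporting the usual interval treats the chosen model as if it had been fixed beforehand. In 30 women the residual variance of the selected model tends to be too small, so intervals are too narrow and p-values too low. Selection runs per outcome, so pain intensity, PPT and PPTo may each carry a different adjustment, which makes arm effects hard to compare.
- **Omitted strata.** Stratified allocation balances the arms on factors that may predict outcome. If they do predict it and the model leaves them out, their variance stays in the error term. The test is then somewhat conservative and the stratification is partly wasted.

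The article says the results will inform the design and sample size of later studies, so miscalibrated intervals and residual variances would be carried forward.

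**Working it through.** **Inputs.** From the protocol article: 15 per arm, difference 19, SD 20, alpha 0.05, six strata (3 degrees of freedom if additive). Assumed, because the article gives no figures: the share of variance explained by the strata, the pre–post correlation, and the number of candidate covariates.

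**1. The plan's own figure.** Two-sided two-sample t-test, noncentrality λ = (19/20) × √(15/2) = 0.95 × 2.739 = 2.602, 30 − 2 = 28 df, critical value 2.048. Power is 70.9%, which reproduces the stated 71%.

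**2. Cost of keeping the strata if they explain nothing.** Take d = 0.95 on the baseline-adjusted scale (assumption).
- Arm + baseline: 30 − 3 = 27 df, power 70.8%.
- Arm + baseline + strata: 27 − 3 = 24 df, power 70.4%.

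The cost is 0.4 points.

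**3. Gain if the strata are prognostic.** What counts is the partial R² after the baseline score. Suppose the strata explain a share s of the variance equally before and after, with within-stratum pre–post correlation r. The overall correlation is ρ = s + r(1 − s), and partial R² = 1 − (1 − s)(1 − r²)/(1 − ρ²).
- s = 0.3, r = 0.5: ρ = 0.65; partial R² = 1 − 0.525/0.5775 = 0.09.
- s = 0.1, r = 0.9: ρ = 0.91; partial R² = 1 − 0.171/0.1719 = 0.005.

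So strata explaining 10–30% of raw variance leave about 0.5–9% once baseline is in the model. With λ = 2.602/√(1 − partial R²) and 24 df:

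| Partial R² | λ | Power with strata | Power without |
|---|---|---|---|
| 0 | 2.602 | 70.4% | 70.8% |
| 0.005 | 2.608 | 70.6% | 70.8% |
| 0.09 | 2.727 | 74.4% | 70.8% |
| 0.10 | 2.742 | 74.9% | 70.8% |

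**4. Selection, baseline kept.** Simulation with 30 women, baseline always in the model, and AIC or BIC choice among the other covariates. The true size of the nominal 5% arm test is about 5–6% with two candidates and about 6–9% with four to six.

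**5. Selection, interval coverage.** A second simulation used blocks of 2 within the six strata, backward AIC or BIC selection, extra covariates unrelated to outcome and, as a simplification, no baseline score. Coverage of the nominal 95% interval for the arm effect:

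| Model | Coverage |
|---|---|
| Strata fixed, no selection | 94.6–95.8% |
| Selection among the two stratification factors only | 94.5–95.3% |
| Selection, 5 extra candidates | 91.5–93.7% |
| Selection, 10 extra candidates | about 86–90% |
| Strata forced in, 5 extra candidates still selected | 92–94% |
| Strata forced in, 10 extra candidates still selected | 87–89% |

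Forcing the strata in while still selecting the rest does not restore coverage.

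**6. Group-by-time contrast.** In a balanced random-intercept model this contrast is within person, so a time-invariant main effect such as chief complaint or age band does not alter it. In three simulated data sets (30 women, three times, strong strata effects) the estimate was identical with and without the strata, and the standard error agreed to four decimals.

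**The case against.** The strongest reply is that little is at stake. The trial is an exploratory pilot, p-values are to be read as graded evidence, the plan says only that covariates may be dropped, and AIC or BIC tends to keep a factor that really predicts outcome. In simulation without the baseline score, with strata explaining 30% of variance, selected models reached 82–85% power against 85% with the strata fixed. With only the two stratification factors as candidates, selection does almost no harm. All this stands and sets the severity, but it does not remove the undercoverage once several covariates are screened.

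Three stronger readings are tempting and are not supported.

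- **That omitting the strata costs some 10 points of power or more.** An arm-only comparison suggests this: 70.9% against 84.8% if the strata explain 30% of variance. The plan's simplest model already contains the baseline score, which absorbs much of any stratum difference in level. The gain then falls to about 4 points at most over the range examined, and the balanced group-by-time contrast gains essentially nothing.
- **That the plan excludes the stratification factors.** That is certain only for the opening model. Age may enter as a demographic, and the list is given by example. The accurate statement is that neither factor is named or guaranteed.
- **That chief complaint must be strongly prognostic because the EIH site follows the diagnosis.** EIH is a pre–post difference, so stratum level cancels, and it is the outcome of the objective 2 models. The dropping rule belongs to objective 1, whose outcomes are pain intensity, PPT and PPTo.

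Nor is this only a detail left to a fuller document: the article states a data-driven dropping rule that, as worded, does not spare the factors it stratified on.

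**Conclusion.** The point holds in a limited form. The selection effect is the firmer part: size about 6–9% instead of 5% with four to six candidates, close to nominal with two. It rests on an assumed number of candidates and on single-outcome linear models that simplify the planned mixed models, so the figures show direction and rough size. It applies to between-arm comparisons at an endpoint, and time-invariant covariates hardly touch a balanced group-by-time contrast; random slopes, missing data or stratum-by-time terms could change that and were not examined.

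The omitted-strata effect is conditional: about 71% against 75% power at a partial R² near 10% beyond baseline, and nothing near zero. The two effects oppose each other and arise in different models, so they should not be added together. Severity is low given the exploratory pilot, but the correction is nearly free.

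**What to change.** In Analyses plan (3.7), state that chief complaint and age band stay as fixed covariates, with the baseline score, in every arm comparison and are exempt from the AIC/BIC dropping rule. Report this prespecified model as the main result for each outcome. Show models with further demographic or psychosocial covariates only as sensitivity analyses, using one common set across outcomes.

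Both parts are needed, because protecting the strata alone leaves the selection problem in place. The change is wording only, since both factors are known at randomisation. It uses up to 3 degrees of freedom (one fewer if age enters as continuous) and costs under 1 point of power if the strata turn out not to be prognostic.

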To determine the clinical significance of EIH (objective (3)), distribution‐based and anchor‐based methods will be performed after the two modalities of exercise. Using distribution based‐methods, ES will be calculated and will be classified following Cohen's *d* formula and interpretation (large ES if >0.8; moderate, >0.5; small >0.2) (Cohen, 1988), if the data are parametric, and by Cliff's Delta, if the data are non‐parametric (Macbeth et al., 2011). Other distribution‐based methods such as those derived from standard deviation and ESs will be explored (Armijo‐Olivo et al., 2022).

The MID of the outcomes of interest (PPTs and PPTo) for EIH using the GRCS as anchor will be used (anchor‐based methods). Participants will be classified as having no improvement when their responses to the GRCS are between −7 and 0, slight improvement between 1 and 3, moderate improvement between 4 and 5, and large improvement between 6 and 7 after the treatment. Changes from baseline to after intervention and 15 min will be calculated for each one of the outcomes of interest at each of the time points collected and used for analysis. Correlations between the GRCS and each of the variables of interest will be tested. The receiver operating curve analysis will be performed to generate the MIDs. This analysis compares the values of each measure from both groups according to the GRCS: participants who did and did not show minimal improvement after treatment. This method constructs a graph of the measures’ performance in classifying the groups for each possible cut‐off point and calculates the sensitivity and specificity for all the cut‐offs. The main analysis will concentrate on calculating the minimal improvement to calculate the MIDs and differentiate the groups. Secondary analysis will include moderate and large improvement when possible. In addition, and if possible, an analysis divided by motor areas (primary and non‐primary) for each group (neck or aerobic) and each diagnosis (TMD, neck only, and both) will be addressed.

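### The anchor-based MID of EIH is an ROC cut-off from at most 30 women, produced whatever the anchor correlation, with women who worsened in the reference group

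*Protocol article*

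**What the plan says.** The third objective in section 2 is to establish the clinical significance of EIH by calculating its MID with distribution-based and anchor-based methods.

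The anchor-based part is in section 3.7:

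- Anchor check: "Correlations between the GRCS and each of the variables of interest will be tested". No minimum value is given, and no consequence if the correlation is weak or in the wrong direction.
- Estimator: "The receiver operating curve analysis will be performed to generate the MIDs". The main contrast is minimal improvement against none.
- Reference group: "Participants will be classified as having no improvement when their responses to the GRCS are between" −7 and 0. The section on self-perception of improvement describes the GRCS as recording deterioration as well as improvement.
- Subgroups: where feasible, a further analysis by area "for each group (neck or aerobic) and each diagnosis (TMD, neck only, and both) will be addressed".

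On size, section 3.2 says: "This exploratory study pilot will initially target 30 participants (15 per group), aiming to gain insights and assess feasibility". It adds that "a formal sample size calculation was not conducted". The one power figure given there concerns the pain VAS. Section 3.6.4 takes EIH at the occipital site for neck pain and at the masseter for TMD, so a site-specific MID may rest on fewer than 30 women.

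**The concern.** An ROC cut-off is the point where an empirical curve happens to peak. In a small sample that point moves a great deal from one sample to the next. An ROC analysis also returns a cut-off whether or not the anchor is related to the outcome, so the correlation needs to be a condition for the analysis and not only a reported result.

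The reference group adds a bias. A MID for improvement should separate slightly better from unchanged. If women who got worse are counted as unchanged, the mean of the reference group falls and the threshold falls with it.

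At stake is objective 3. The resulting values, in units of pressure pain threshold (PPT) or tolerance (PPTo), could be used to judge later exercise studies.

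**Working it through.** **The plan's own figure.** Section 3.2 gives 71% power for a 19-point difference with SD 20 and 15 per group at 0.05. Here d = 19/20 = 0.95, the noncentrality is 0.95 × √(15/2) = 2.60, and df = 28. The two-sided t-test then has 70.9% power, so the figure reproduces. It concerns a between-group difference in pain and says nothing about the precision of a MID. The documents give no figure for that, so it was simulated.

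**Inputs.** From the documents: N = 30; GRCS dichotomised at improved versus not; ROC cut-off as estimator. Assumed, because the documents do not give them: the separation between improved and unimproved women, the strength of the anchor, and the proportion improved.

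**Step 1: precision at N = 30.** Change scores are normal with SD 1, with 15 improved and 15 not, and 4000 trials per setting. The ROC cut-off maximises Youden's J = sensitivity + specificity − 1. The logistic MID is the change at which the fitted probability of improvement equals the observed proportion improved, (logit p − a)/b. For d = 0.5 the true midpoint is 0.25 SD.

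| Setting | ROC cut-off: SD (95% range) | Logistic MID: SD (95% range) |
|---|---|---|
| d = 0.5, 15/15 | 0.65 (−1.15 to 1.34) | 0.18 (−0.10 to 0.62) |
| d = 0.8, 15/15 | 0.53 | 0.18 |
| 20/10 split | 0.66 | 0.19 |

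The logistic SDs are robust SDs. Repeat runs at d = 0.5 gave ROC SDs of 0.64 and 0.66. The gap stays large with unequal variances or skewed data.

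**Step 2: a second model.** Change score and anchor are bivariate normal, half the women improved, and cut-offs are centred on the mean change.

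- N = 30, r = 0.3: SD 0.63, 95% range −1.26 to 1.22.
- N = 30, r = 0.5: SD 0.48, 95% range −0.99 to 0.93, a width of 0.93 + 0.99 = 1.92 SD.
- N = 15, r = 0.3: −1.48 to 1.37; r = 0.5: −1.18 to 1.14.
- Three sessions pooled and treated as 90 independent observations, which is optimistic: SD 0.49 for r = 0.3 and 0.35 for r = 0.5.

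**Step 3: an unrelated anchor (r = 0).** At N = 30 a cut-off is still returned, with SD 0.99 and range −2.09 to 1.75. The AUC reaches 0.70 by chance in 4% of analyses at N = 30, 12% at N = 15 and 26% at N = 5. The logistic MID is no safer by itself: with d = 0 its range is −0.36 to 0.33, a precise-looking number centred on the mean change. A condition on the correlation is therefore needed with either estimator.

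**Step 4: what a correlation condition achieves.** If r must be at least +0.30, an unrelated anchor passes by chance in 5.4% of analyses at N = 30, 13.9% at N = 15, 20.0% at N = 10 and 31.2% at N = 5. Using |r| at N = 30 doubles this to 10.7%, because wrong-direction correlations also pass.

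**Step 5: women who worsened.** Illustration: improved women have mean 0.5 and unchanged women mean 0; suppose 3 of the 15 reference women worsened by 0.8 SD. The reference mean is (12 × 0 − 3 × 0.8)/15 = −0.16. The midpoint moves from (0.5 + 0)/2 = 0.25 to (0.5 − 0.16)/2 = 0.17, a fall of 0.08/0.25 = 32%. The direction is general when the GRCS tracks PPT. The size depends on the assumed 3 of 15 and 0.8 SD.

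**Step 6: subgroups.** Two arms by three diagnoses make 6 cells of participants; 30/6 = 5 women per cell if evenly spread (assumption). At N = 5, with r from 0 to 0.5 and 30% to 70% improved, 6% to 18% of cells have everyone or no one improved, so no ROC curve exists.

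**The case against.** The trial is an exploratory pilot meant to inform later studies, and ROC is a recognised way to obtain a MID. The article may condense a fuller analysis plan that contains a correlation threshold. The pilot label softens the point, but calculating the MID is a stated objective, and the article itself fixes both the ROC step and the −7 to 0 grouping.

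Several stronger readings are tempting, and the documents do not support them:

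- *The anchor is never checked.* It is: correlations are tested. What the text lacks is a threshold and a consequence.
- *A separate cut-off is derived at every session.* Changes are calculated at each time point and used for analysis, but the text does not say whether the ROC is run per session or pooled.
- *The MID will be read from a dozen tiny cells.* The subgroup analysis is conditional on feasibility and is not said to be ROC. If the areas are body sites measured in every woman, there are 6 participant cells.
- *The distribution-based arm gives no threshold in pressure units.* Effect size is the first method named, but section 3.7 also foresees methods derived from the standard deviation.

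The logistic alternative also deserves caution. The main comparison uses data in which its model is exactly true, and it too returns a number when the anchor is unrelated. The first caveat is eased by the unequal-variance, skewed and 20/10 checks. The second stands, which is why the correlation condition belongs in the fix.

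**Conclusion.** The concern holds for the main anchor-based analysis. With at most 30 women, and assumed separations of 0.5 to 0.8 SD, the ROC cut-off has a sampling SD of about 0.5 to 0.65 SD of the change score; a logistic MID on the same data has about 0.2 SD. Nothing in the text stops a MID from being derived when the anchor is weak. The reference group includes women who worsened, which biases the MID downward if the GRCS tracks PPT, by an amount that the documents do not determine.

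A reader might infer that the published MID will be mostly noise or will have the wrong sign. Neither is established. The first is fair for an anchor near r = 0 and in the subgroups; at N = 30 with r = 0.5 the cut-off is very imprecise but still carries information. The second depends on the mean change in unimproved women, which is not given.

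**What to change.** All changes are to the analysis wording:

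1. Make the logistic predictive-modelling MID the main anchor-based estimate for each EIH site, pooling sessions and arms, with a 95% interval from a bootstrap that resamples participants. Keep the ROC cut-off, with its own bootstrap interval, as a sensitivity analysis.
2. Use GRCS 0 (unchanged) as the reference in the main contrast, and run the −7 to 0 grouping as a sensitivity analysis.
3. Derive an anchor-based MID only if the GRCS correlates with the PPT or PPTo change in the expected direction, for example Spearman r of at least +0.30. Otherwise report it as not estimable.
4. Drop the arm-by-diagnosis MIDs or label them descriptive.

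Optionally, name 0.5 SD of the pre-exercise value as the SD-based method already foreseen. A standard error of measurement from the duplicate readings can be added for PPT only, because section 3.6.3 has PPTo measured once per site.

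**Cost.** A bootstrap and revised text; no extra visits or measurements. The method assumes a logit-linear relation and one MID across sessions and arms, although the sessions were chosen to differ in intensity. A few women leave the main contrast. The MID may end up not estimable: at N = 30 a true correlation of 0.3 would pass the threshold only about 46% of the time.
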